#### Exploratory efficacy analyses

Further exploratory analyses of the primary endpoint may be conducted to identify and better understand any correlations between selected demographic, baseline characteristics, and response status using logistic regression techniques. Exploratory analyses of changes in positive affect, negative affect, hedonic tone, cognitive, and overall functioning, meaningfulness of life and happiness and patient functioning as measured by LAPS will be performed. Furthermore, exploratory analyses will be carried out with the aim to assess the resource consumption associated to VNS therapy for DTD management per patient; this will include hospitalizations, antidepressant medication usage and adjunctive antidepressant treatments pre and post VNS Therapy. For those patients who provide consent to collect additional data and who are enrolled in a country with a national healthcare database, a more detailed resources consumption analysis will be conducted.

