**Fig. 1 Fig1:**
[figure not shown]
schematic representation of the VNS therapy system. Study participants will be implanted with the VNS Therapy system that includes a small pulse generator surgically implanted subcutaneously in the thoracic area (usually the left side) and a thin, flexible wire called a lead that connects to the vagus nerve (Fig 1). Mild intermittent electrical stimulation is delivered to the vagus nerve eliciting action potentials in the vagal fibres that synapse in the brainstem. Clinicians are able to program the system using an external programming device relying on attentive patient-specific titration to select the right combination of adjustable parameters (output current, frequency, pulse width, and signal ON and OFF times) to attain full activation of the vagus nerve while minimizing stimulation-induced side effects. Additional information is provided in the VNS Therapy Physician’s Manual and the Implant Manual

The stimulation of the left vagus nerve has been shown to induce widespread bilateral effects in areas of the brain implicated in affective regulations that are also responsible for modulation of key neurotransmitters such as serotonin and norepinephrine.

Several large clinical studies have evaluated VNS Therapy in patients with depression since the market approval and have shown that the treatment is efficacious for long-term patient management; and a meta-analysis demonstrated that VNS has an acceptable adverse event profile [25–28]. These studies also demonstrated that the assessment of depression outcomes has to be longitudinal and of sufficient duration an improved clinical response is observed within 6 to 24 months following implantation with the mean time-to-first response of 12 months (defined as a 50% reduction in baseline depression assessment scores). Additional studies of VNS Therapy in the treatment of depression suggest that: (1) VNS Therapy has a positive effect on overall mortality and suicidality in DTD [29]; (2) VNS Therapy has clinically meaningful improvements in quality of life in patients with unipolar as well as bipolar disorder, even when the response is below the classic 50% reduction from baseline score [30]; (3) VNS Therapy improves cognitive and clinical measures in DTD [31]; (4) VNS Therapy is associated with localized changes in the brain as evidenced by functional brain imaging techniques [32]; and (5) patients who fail ECT may respond to VNS [33].

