**Secondary outcome measures**	
Duration of response	The difference between the first recorded date of post-baseline MADRS score when response is achieved (based on a decrease in baseline MADRS score of ≥50%) and the first date at which the MADRS score reaches a level of < 40% from baseline.
Duration of response	Change in MADRS score over time
Duration of response	Cumulative percentage of first-time responders (based on reduction in baseline MADRS score of ≥50%) and cumulative remission (based on MADRS score of ≤9 at any post-baseline visit) over time.
Changes in mood, depression, and mania scores	This will be based on changes in MADRS, QIDS-SR, and ASRM. The QIDS-SR questionnaire measures symptoms of mood and depression [41]. The ASRM measures the presence and severity of manic and hypomanic symptoms, specifically in patients diagnosed with bipolar disorder [42]. Note: ASRM is an optional assessment.
Changes in quality of life and psychosocial impairment	The WPAI:D questionnaire measures impairments in work and activities in depression [43]. The Q-LES-Q-SF scale measures the degree of enjoyment and satisfaction experienced during the past week [44]. The EQ-5D-5L questionnaire measures generic health status and quality of life [45].
Changes in suicidality	Based on Item Number 10 of MADRS and Item Number 12 of QIDS-SR.
Changes in antidepressant treatments	This will include data on drug dosage and type of antidepressant medications, and duration and intervals of maintenance ECT, rTMS, and/or psychotherapy.
Changes in cognition	THINC-it® Tool includes the 5-item PDQ-5, in addition to 4 traditional cognitive assessments which have been reconfigured for computer-based administration. Thus, it assesses both a patient’s subjective assessment as well as key objective measures of cognitive function [46]. Note: THINC-it is an optional assessment.
Changes in anxiety	The GAD-7 measures severity of generalized anxiety disorder [47]. Note: GAD-7 is an optional assessment.

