### Sample size and statistical analysis considerations

As this is an observational study designed to describe the characteristics of VNS Therapy in a real-world setting, the statistical analysis of the study outcomes will focus on a combination of descriptive and exploratory statistics, rather than confirmation of formal hypothesis testing; that is, the provision of two-sided 95% confidence intervals rather than *p*-values. As an additional consequence, the emphasis provided in the study will be on the precision of the estimate. A sample size of 500 patients is sufficient to provide higher precision of the estimates in term of width of the 95% confidence interval for the key study endpoints:
For the primary endpoint based on MADRS, the width of the 95% CI will be of 7.8% assuming an observed response of approximately 25%.For the secondary endpoint based on Q-LES-Q-SF response (and the available Q-LES-Q-SF data obtained in the D-23 study), the width of the 95% CI will be 8.9% assuming an observed response of approximately 50% [49].

Enrolled analysis population will include all participants who signed the informed consent and who satisfy the study eligibility criteria. Safety analysis population will include all enrolled participants who were implanted with the VNS Therapy system and received at least one dose of stimulation. The full analysis set population will include all participants in the safety analysis population with evaluable baseline device data; that is, patients who have the device implanted and received at least one dose of stimulation. As such, for this study, the full analysis set population is equivalent to the safety analysis population.

The full analysis set population will be used mainly for all effectiveness and efficiency summaries and is considered the primary population. Descriptive statistics will be calculated using as reference the number of participants in the relevant analysis population, according to the nature of the data (i.e., continuous, discrete, time to event) as follows: continuous variables by number of non-missing observations, arithmetic mean, standard deviation, minimum and maximum values, median and quartiles and categorical variables by absolute and relative frequencies.

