#### Primary analysis

The primary endpoint of response ─ defined as a decrease in MADRS total score of at least 50% from baseline to 12 months post-implant ─ will be provided for patients who were experiencing a major depressive episode at the time of enrolment (i.e. a baseline MADRS total score ≥ 20). The number and percentage of participants with response and the associated 95% confidence interval will be presented.

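### The one method named for relating baseline characteristics to outcome, logistic regression on the 50% MADRS response, is valid but inefficient; a model of the MADRS score is a cheap addition

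*Protocol article*

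**What the plan says.** Exploratory efficacy analyses opens with an optional step: "Further exploratory analyses of the primary endpoint may be conducted to identify and better understand any correlations". The correlations in question are "correlations between selected demographic, baseline characteristics, and response status using logistic regression techniques". Response is the primary endpoint, which Primary analysis gives as "defined as a decrease in MADRS total score of at least 50% from baseline to 12 months post-implant", reported for patients with a baseline MADRS total of 20 or more.

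The score behind the cut is available throughout. Table 1 schedules the MADRS at baseline and at every follow-up visit, and Table 2 lists "Change in MADRS score over time" among the secondary outcomes. For the continuous secondary endpoints, Secondary efficacy analyses describes visit-by-visit summaries and 95% confidence intervals for the changes. No section of the article relates a baseline characteristic to the MADRS score itself.

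Sample size and statistical analysis considerations sets the style of inference, "the provision of two-sided 95% confidence intervals rather than" p-values, and puts the emphasis on precision. Its planning figure for the primary endpoint is "the width of the 95% CI will be of 7.8% assuming an observed response of approximately 25" per cent, with 500 patients.

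**The concern.** Cutting a continuous change at 50% treats a patient who improves by 5% and one who improves by 45% as the same. The further the cut lies from the middle of the distribution, the more is lost, and a 25% response rate puts it well off centre. The Background, in the paragraph on earlier VNS studies, reports quality-of-life gains "even when the response is below the classic 50% reduction from baseline score", so the plan itself regards some change below the cut as worth noting.

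At stake is the precision of the predictor estimates. The Discussion expects a heterogeneous population and attrition, and the primary analysis is limited to a baseline MADRS of 20 or more. The number usable at 12 months may therefore be below 500, which makes an efficient analysis more valuable. No primary or secondary result is affected.

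**Working it through.** **Inputs from the article.** N = 500; assumed response rate p = 0.25; two-sided 95% intervals. All come from Sample size and statistical analysis considerations.

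**Reproducing the plan's own figures.** The exact (Clopper-Pearson) interval with N = 500 has a width of 7.77% at p = 0.25 and 8.94% at p = 0.50. These match the stated 7.8% and 8.9%. The simple Wald formula gives 7.59% and 8.77%. The stated precision is therefore sound, and p = 0.25 with N = 500 can be carried forward.

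**Information kept by the cut.** Assume a normal outcome and a weak predictor that shifts its mean. The efficiency of the binary outcome relative to the continuous one is then

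ARE = φ(z_p)² / [p(1 − p)],

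where φ is the standard normal density at the cut. At p = 0.25, z = 0.674 and φ(z) = 0.3178, so ARE = 0.1010 / 0.1875 = 0.539. The loss is 1 − 0.539 = 46%. The effective sample is 500 × 0.539 ≈ 269 patients. Interval widths grow by 1/√0.539 = 1.36.

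The same calculation at other response rates:

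| Response rate | ARE | Information lost | Effective N of 500 | Intervals wider by |
|---|---|---|---|---|
| 20% | 0.490 | 51% | 245 | 43% |
| 25% | 0.539 | 46% | 269 | 36% |
| 30% | 0.576 | 42% | 288 | 32% |
| 40% | 0.622 | 38% | 311 | 27% |
| 50% | 0.637 | 36% | 318 | 25% |

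The last column compares both models on an equivalent scale, since log odds ratios and MADRS points are not directly comparable.

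**Simulation check.** With N = 500, one predictor correlated 0.12 with a normal outcome, a 25% cut and 2,000 runs, the squared ratio of mean z-values (logistic to linear) was 0.52. That is a loss of about 48%, close to the formula. At two-sided 5%, power was 78% for the linear model and 51% for the logistic model.

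**Binary predictor.** Take a predictor present in half of 500 patients, with an assumed effect of 0.25 SD. The linear z is 0.25 × √(500 × 0.25) = 2.80, giving power Φ(2.80 − 1.96) ≈ 80%. The logistic z is 2.80 × √0.539 ≈ 2.05, giving about 54%. In simulations over assumed effects of 0.20 to 0.30 SD, prevalences of 25% and 50%, and N of 400 and 500, the linear model gained 13 to 26 percentage points.

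The effect sizes, correlation and prevalences are illustrative; none is in the article.

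**The case against.** **The analysis is optional, and the article is a condensed account.** The sentence says such work may be done, names no covariates and excludes nothing. A reader might infer that the plan commits itself to the binary model and rules out a continuous one. The text does not support that, and a full protocol or SAP could contain such a model. What stands is narrower: the article does name an outcome form and a method, and that stated choice can be improved.

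**The method fits its object.** The sentence concerns the primary endpoint, which is binary, and logistic regression is the standard model for it. This is right. A model of the score answers a related but different question, so it is an addition and corrects no error.

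**Power is not the plan's criterion.** This is also right. The plan reports intervals, so the comparison of widths is the relevant measure and the power figures only illustrate it.

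**The 46% depends on a model.** It assumes normality, weak mean-shift effects and 25% response. It also compares a cut with the same underlying variable, whereas the cut here is on percentage change and the proposed model uses the 12-month total adjusted for baseline. The figure therefore does not measure the gain from the fix exactly. A simulation of that model, under assumed MADRS distributions, gave about 81% against 56% power at N = 500. This agrees in direction and rough size but rests on unverified inputs.

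**Predictors are not a stated aim.** Neither Study aims nor Table 2 lists them, which limits the priority of the point.

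**Conclusion.** The point holds as a low-priority, inexpensive improvement. The only method named for relating baseline characteristics to outcome is valid but inefficient. At the plan's 25% response rate it loses about 46% of the information (36% to 51% for response rates from 50% down to 20%), with intervals about 36% wider on an equivalent scale (25% to 43%). These sizes rest on an approximately normal outcome and weak predictors; the article gives no MADRS distribution or standard deviation.

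Four stronger readings are not supported:

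- That the responder rate or its confidence interval is wrong. The descriptive primary analysis is untouched, and its planned precision reproduces.
- That most of the differences between patients are lost. At 25% response the loss is under half.
- That either model would show who benefits from VNS. There is no control group, so both identify predictors of outcome under VNS with concomitant treatment, not of an effect caused by VNS.
- That the Background calls all improvement below 50% clinically meaningful. Its statement is about quality of life.

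**What to change.** In Exploratory efficacy analyses, add a linear model of the 12-month MADRS total score, or a mixed model over visits, adjusted for baseline MADRS and using the same selected characteristics. Report each effect in MADRS points with a 95% confidence interval. Keep the logistic model of response status as the companion result in responder terms. Describe both sets of results as predictors of outcome under adjunctive VNS.

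The cost is one added model, with no new data and no extra patients. The downsides are results on two scales and a check of the residuals. The primary endpoint and its analysis stay as they are.

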#### Safety analysis

Safety data will be summarized descriptively, based on the safety analysis population (defined above). Adverse event data will be summarized by means of number of participants with at least one event, incidence rates, crude incidence rates. Similarly, statistics for serious adverse event; adverse device effect; serious adverse device effect; unanticipated serious adverse device effect and deaths will be presented.

Note that an adverse event with a ‘related’ causal relationship to the VNS therapy will be considered an Adverse Device Effect. Details of any recorded device deficiencies will be listed. Further safety tabulations may be presented, as appropriate.

#### Interim analysis

An interim analysis may be planned after a sufficient number of patients have enrolled into the study.

### Data monitoring

The principal investigators will oversee their respective centres, while the sponsor’s study manager will oversee both the scientific and administrative aspects of RESTORE-LIFE. The principal investigators will communicate regularly with the sponsor’s study manager regarding data collection, and the project coordinator will ensure smooth internal and external communications.

### Study steering committee

A steering committee has been established for this study to assist the sponsor in designing and managing the study based upon scientific, medical, and technical experience and expertise. The committee is comprised of individuals with specialized knowledge and experience in psychiatry and/or any other discipline needed to fulfil the responsibilities of the steering committee.

## Discussion

This paper describes the study protocol for RESTORE-LIFE: a prospective, observational, multi-site, global post-market study intended to assess short-, mid-, and long-term effectiveness and efficiency outcomes in ‘real-world’ setting among patients with DTD treated with VNS Therapy as adjunctive therapy.

To our knowledge, RESTORE-LIFE will be the largest post-market trial with VNS Therapy in DTD to be conducted globally.

The study has several strengths, it is multicentre and has been designed to evaluate if VNS Therapy meaningfully improves and sustains clinical and depressive symptom outcomes in patients with DTD. The study will also investigate the durability of VNS response in DTD and the long-term disease management of patients with DTD treated with VNS. In addition, the study results will potentially clarify clinical, functional, and health economics questions in a real-world patient population with DTD in different countries around the world. Changes in positive affect, negative affect, hedonic tone, cognitive functioning, overall functioning, meaningfulness of life, and happiness will also be assessed.

We anticipate that the study participants may benefit from more frequent visits with their treating physician. In addition, patients receiving VNS Therapy in the future may benefit from information gathered during this study outside the standard of care.

Currently there is no standard approach to the management of DTD as a standardized algorithm will not be appropriate for the treatment of such a heterogenous patient population. The results of this study may provide new evidence to influence clinical practice, including potentially providing access to VNS Therapy to patients with DTD in new and/or additional geographical regions, and help healthcare providers make more informed therapeutic decisions in the use of VNS Therapy as an effective and safe adjunctive therapy in treating patients with DTD.

As the study will assess VNS Therapy for the treatment of patients in a real-world setting, it may potentially have several related limitations, including the lack of randomization and blinding of participants and clinicians, the lack of a control group, potential attrition of participants and deviations in the delivery of the intervention, differential optimization of VNS parameter settings, differential use of concomitant anti-depressant medications and treatments in patients, and the heterogeneous study population may limit generalizability. The suicidality assessment may be limited as it will be assessed based on a single item in the MADRS scale and a single item in the QIDS-SR scale, instead of being assessed using a specific suicidality scale. In addition, this will be a 5-year longitudinal study and participant attrition over time may decrease the sample sizes at each analysis time point.

### Study status

Enrolment in the study commenced in December 2017 and is expected to take about 5 years to complete. At the time of submission, participant recruitment and data collection are ongoing with 76 study participants enrolled, and new centres are continuing to be selected for study participation. The RESTORE-LIFE study is running in parallel with a randomized blinded trial of VNS in TRD in the United States (RECOVER trial; ClinicalTrials.gov identifier NCT03887715) [50].

## Data Availability

No data is available at the time of submission as the study is in enrolment phase. After the dataset has been locked, the data will be available from the study sponsor LivaNova on reasonable request.

## Abbreviations

ASRM: Altman Self-Rating Mania Scale
ATHF: Antidepressant Treatment History Form
CE Marking: Conformité Européene (European Conformity)
DTD: Difficult-to-Treat Depression
ECT: Electroconvulsive Therapy
EQ-5D-5L: EuroQoL five dimensions questionnaire
FDA: Food and Drug Administration
GAD-7: Generalized Anxiety Disorder Assessment
LAPS: Leuven Affect and Pleasure Scale
MADRS: Montgomery Åsberg Depression Rating Scale
MINI: Mini-International Neuropsychiatric Interview
PDQ-5: Perceived Deficits Questionnaire
QIDS-SR: Quick Inventory of Depressive Symptomatology Self-Report
Q-LES-Q-SF: Quality of Life Enjoyment and Satisfaction Questionnaire – Short Form
rTMS: repetitive Transcranial Magnetic Stimulation
TAU: treatment-as-usual
THINC-it: THINC-Integrated Tool
TRD: Treatment-Resistant Depression
VNS: Vagus Nerve Stimulation
WPAI:D: Work Productivity and Activity Impairment Questionnaire-Depression
